### Procedure

Initially, intake clinicians working at the youth mental services will identify individuals eligible to participate in the study through assessments conducted as part of their normal triage protocol. This includes a structured face-to-face assessment of psychosocial and mental health problems, which provides the information necessary to determine eligibility based on the criteria listed [39]. The study will be introduced to eligible individuals, who will then be screened for the presence of at least moderate depressive symptoms using the DASS-21 depression subscale [38] and provided with the plain language statement. Permission for a member of the research team to contact them will be sought. A member of the research team will then contact them to discuss the details of the study further and answer any questions they may have. If the individuals agree to participate, informed consent will be sought and participants will be randomized into one of the treatment conditions.

### Randomization

Participants will be randomized to conditions using an adaptive biased-coin approach, the ‘urn design’ [40]. In an urn design, the probability of assignment to a group begins at 1:1, and is subsequently based on the magnitude of imbalance between groups. If the allocation ratio is found to be too far in one group’s favour then the probability is altered to increase the odds of allocation to the smaller group until this imbalance is rectified. This approach was chosen so as to counteract the risk of unequal group sizes, whilst still preserving most of the unpredictability of simple randomization. Randomization will be performed by a third-party outside of the research team using the online software Research Randomizer Version 3.0 [41].

### Sample size

Sample size was calculated using GPower 3 [42], with two aims of the current study under consideration: whether participants in the cognitive-reminiscence therapy group report improvements on measures over time, and whether these effects differ from those achieved by usual care. Although previous evaluations of this intervention with older adults have produced large effect sizes; [21-23], it was decided to err on a somewhat more conservative side and estimate a sample size for a moderate-to-large within-group effect over time. It was calculated that using a repeated-measures within-subject analysis of variance (ANOVA) across five time-points with an α level set at 0.05 (two-tailed), statistical power level (1 − β) of 0.80, and an estimate of correlation among repeated measures of 0.5, 15 participants will be needed in the cognitive-reminiscence group to detect this effect. To assess for a small-to-moderate interaction effect between groups and time using the parameters described above, a total of 32 participants (16 per group) will be needed. After factoring in the average dropout rate of 20% for reminiscence-based therapies [20], it is estimated that a minimum of 19 participants per group (total *N* = 38) will need to be recruited to assess within-group effects and differences between groups in treatment effects.

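### The recruitment target of 19 per group leaves about 15, not the required 16, after the plan's own 20% dropout; its inputs give 20 per group (40 in total), a minor arithmetic slip

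*Protocol article*

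**What the plan says.** The Sample size section of the protocol article sizes the trial for two aims.

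- **Within-group aim.** The authors chose to "estimate a sample size for a moderate-to-large within-group effect over time", using a "repeated-measures within-subject analysis of variance (ANOVA) across five time-points" with two-tailed alpha 0.05, "statistical power level (1 − β) of 0.80" and "an estimate of correlation among repeated measures of 0.5". The result is that "15 participants will be needed in the cognitive-reminiscence group to detect this effect".
- **Between-group aim.** For a small-to-moderate group-by-time interaction with the same parameters, "a total of 32 participants (16 per group) will be needed".

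The section then makes its dropout allowance: "After factoring in the average dropout rate of 20% for reminiscence-based therapies [20], it is estimated that a minimum of 19 participants per group", giving 38 in total. The same sentence says that this number is meant to serve both aims.

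The Analysis section plans repeated-measures ANOVAs and an intention-to-treat analysis of post-treatment data with imputation of missing values. The Discussion names the small sample as perhaps the most important limitation.

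**The concern.** The larger of the two per-group requirements is 16, so a target that covers both aims must leave at least 16 per group after the assumed dropout. Nineteen per group does not. The section therefore contradicts itself on the number that governs recruitment.

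What is at stake is the stated 0.80 power for the group-by-time test. That test is the randomised comparison with usual care and answers the second of the two questions posed in the Background. The within-group aim is not affected, because 15.2 still covers its requirement of 15.

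**Working it through.** **Inputs, all from the Sample size section:** 15 needed in the cognitive-reminiscence group (within-group aim); 16 per group, 32 in total (interaction aim); dropout d = 0.20; five time-points (m = 5); correlation ρ = 0.5; alpha 0.05; power 0.80. Neither effect size is given as a number.

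**Step 1. The figures before dropout reproduce.** Take the usual repeated-measures ANOVA calculation with sphericity: noncentrality λ = f² × N × m/(1 − ρ), numerator df = m − 1 = 4, and denominator df = (N − k)(m − 1) for k groups.

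- Within-group, k = 1, assumed f = 0.30: n = 15 gives power 0.817 and n = 14 gives 0.783, so 15 is the minimum.
- Interaction, k = 2, assumed f = 0.20: N = 32 gives λ = 0.04 × 32 × 5/0.5 = 12.8, df 4 and 120, power 0.814. N = 30 gives λ = 12.0, df 4 and 112, power 0.783. So 32 is the smallest even total that reaches 0.80.

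The requirements of 15 and 32 are therefore sound under these assumed values of f.

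**Step 2. Where 19 could come from.**

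- 15/(1 − 0.20) = 18.75, rounded up to 19. This inflates only the within-group requirement.
- 16 × 1.20 = 19.2, rounded down to 19. This adds 20% of the requirement instead of dividing by the retained fraction. As a minimum it would in any case round up to 20.

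**Step 3. What 19 leaves.**

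- Per group: 19 × 0.80 = 15.2, against 16.
- In total: 38 × 0.80 = 30.4, against 32.
- Largest dropout that still leaves 16 of 19: 3/19 = 15.8%, against the assumed 20%.

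**Step 4. The inflation consistent with the section's inputs.**

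- 16/(1 − 0.20) = 20 per group; 32/(1 − 0.20) = 40 in total.
- Check: 20 × 0.80 = 16 and 40 × 0.80 = 32, exactly the stated need.

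Steps 3 and 4 use only integers printed in the section and need no effect size.

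**Step 5. Effect on power (f is an assumption).** For 32 to be the smallest even total reaching 0.80, f must lie between about 0.197 (power exactly 0.80 at N = 32) and about 0.204 (power reaches 0.80 already at N = 30).

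| Assumed f | Power, N = 32 | Power, N = 30 |
|---|---|---|
| 0.197 (lowest compatible) | 0.80 | 0.769 |
| 0.20 | 0.814 | 0.783 |
| just under 0.204 (highest compatible) | 0.83 | just under 0.80 |

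Against the planned 0.80, the shortfall among 30 completers is 0 to about 3 percentage points. Using 30 is slightly harsh, since expected completers are 30.4; at N = 31 and f = 0.20 power is 0.799.

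**The case against.** The case on the other side concerns size, and most of it stands.

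- **The gap is tiny.** One participant per group and at most about 3 points of power would not change the design. This stands.
- **Completers are not the whole analysis set.** The Analysis section plans intention-to-treat with imputation, and with five time-points many who drop out will have given some data. Under that analysis, power would lie between the completer value (about 0.78 at f = 0.20) and the no-loss value for 38 (about 0.88). This stands as a softening factor, but imputed values do not carry the information of observed ones, and the Sample size section itself chose to allow for dropout by recruiting more. It does not make 19 the right result of that step.
- **The 20% is a rate for reminiscence-based therapies.** No rate for usual care is given. Applying 20% to both groups follows what the article appears to do, and it limits how firmly the loss in the usual-care group can be stated.
- **Nineteen is called a minimum.** Recruiting more is not excluded. But a minimum that falls short of its own requirement is still misstated.

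A reader might infer that the trial fails to deliver 80% power for its randomised comparison, or is seriously underpowered. The document does not support that. The effect size is stated only in words, the compatible range includes values where 30 completers give almost 0.80, and the planned imputation may recover part of the loss.

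**Conclusion.** The target is wrong as written, and the error is minor. From 16 per group and 20% dropout the figure is 20 per group (40 in total), not 19 (38). That is exact arithmetic on numbers in one section. Neither derivation of 19 serves the between-group aim: one inflates only the within-group requirement, and the other uses the wrong operation and rounds a minimum down.

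The consequence is a shortfall of two recruits and a group-by-time power of about 0.77 to just under 0.80 among completers. That range assumes sphericity, 20% dropout in both groups, 30 completers, and an interaction effect f between about 0.197 and 0.204, back-solved from the stated 32.

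**What to change.** Amend one sentence of the Sample size section in one of three ways.

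1. Keep 38 and state that, with 20% dropout, the group-by-time test has slightly less than 80% power among completers (about 77–80%), giving the numerical f assumed.
2. Keep 38 and state that it preserves 16 per group only if dropout is no more than about 16%.
3. Correct the target to 20 per group, 40 in total, showing 16/(1 − 0.20) = 20.

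The first two cost only wording and suit a trial already recruiting (Trial status gives January 2013 as the start). The third costs two further participants. None alters the design, the outcomes or the analysis.

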### Conditions

#### Cognitive-reminiscence

Participants in this group will receive an intervention based on a manualized reminiscence therapy formulated by Watt and Cappeliez [21]. Although the intervention will follow the general protocol of this manual, several distinct adaptations will be made for the current study. Firstly, the original manual described separate but overlapping protocols for integrative and instrumental reminiscence therapy. The current intervention will combine these two approaches, as per Cappeliez [23]. Secondly, the content of the sessions will be organized on the basis of only one participant, rather than a group delivery, for which it was originally designed. Thirdly, the questions used in sessions and on homework sheets to elicit memories will be age-appropriate for young adults and their stage of psychosocial development.

The intervention will be administered on the premises of the participating youth mental health service. The intervention comprises six 60-minute weekly sessions of individual psychotherapy. Over the course of therapy, six different topics are used to stimulate memories as a basis for therapeutic work. These are: turning points, family life, major life works, loves and hates, stressful experiences, and meaning in life. In the first session, rapport is built and psychoeducation is provided on autobiographical memory (specifically, integrative and instrumental types of reminiscence), related depressogenic patterns, and cognitive therapy and stress and coping models of depression. Information is provided about the intervention, including evidence for its effectiveness and what it entails for the participant and therapist. Following this, the first topic, turning points, is discussed, using a list of questions to help stimulate memories. The procedure for therapeutic work then follows the same pattern in each session. Memories are elicited and among these several are identified by the therapist and participant collaboratively as being of importance and to be discussed. The therapist ensures that there is at least one event or experience that is likely to benefit from cognitive therapy techniques and one that relates to stress and coping. These memories are then elaborated on, with the therapist ensuring that sufficient details of the memories are provided so as to promote increases in memory specificity. The respective therapeutic techniques are then utilized where appropriate, for example, restructuring beliefs about perceived failures and negative experiences, focusing on positive experiences and achievements to enhance perceptions of self-worth or self-efficacy, and breaking down previous coping step-by-step and highlighting effective strategies. As a general guideline, the therapist aims to help the individual create a cohesive and positive narrative of their life and a view of themselves that realistically integrates good and bad experiences. Further, therapists orient themselves towards improving clients’ perceptions of their meaning in life, self-esteem, self-efficacy, and optimism, given that these variables have been shown to mediate adaptive reminiscence functions and depressive symptoms [43] and changes produced by reminiscence-based therapies [44,45]. In the first session, a brief problem-solving framework is introduced, and a problem list is elicited for work in subsequent sessions. At the end of the session, a summary is provided and feedback is elicited from the participant on what was learned and any changes that have occurred. A homework sheet is then provided, listing questions related to the next week’s topic. A rationale is provided for this homework sheet, including its usefulness in promoting effective change [46]. The following five sessions follow a similar procedure of reviewing homework on the topic for the week, identifying memories to elaborate on and engaging in therapeutic work with these memories, and utilizing a problem-solving framework to choose solutions to identified problems to implement over the next week. Specific coping strategies that have been discussed in the session are drawn on to assist in the problem-solving work, as well as content related to self-efficacy and approach-coping behaviour that is broadly promoted over the sessions. In the last session, a summary is provided by the therapist of the work completed over the intervention, and the participant is invited to provide feedback of the experience and reflect on any change that has occurred.

Following the completion of the sixth session of therapy, participants will be free to utilize any further services or support that they wish. To ensure adherence to the treatment protocol, the treating therapist will complete a brief checklist following each session, noting whether required components of the therapy were covered in each session.

#### Usual care

Participants in the usual-care condition will receive support following the normal procedures implemented by the clinical pathway coordinator of the participating youth mental health service. There will be no restriction on the type, amount or length of support that is received. Given the service in which the study will be conducted, this support will probably consist of six to ten sessions of evidence-based psychological treatment provided by registered mental health professionals. Information will be collected for each participant on what their usual care constitutes so that it can be described as a group and contrasted with the cognitive-reminiscence group. Following the cessation of data collection, all participants in the usual-care group will be invited to receive the six-week course of cognitive-reminiscence therapy should they wish.

#### Outcome measures

All outcome measures will be completed online via links that are emailed to participants at the relevant time-points. As stated, the time-points will be baseline, three weeks into the intervention, post-intervention, one month post-intervention, and three months post-intervention. Multiple time-points will be used to increase statistical power [47], improve the chance of detecting when significant change occurs, and examine whether treatment effects are maintained following the end of treatment. The demographic information that will be collected from participants will be: age, sex, education, employment status, relationship status and whether or not previous treatment for depression has been received.

#### Primary outcomes

The primary outcome will be depressive symptomatology. To assess for depressive symptoms the seven-item self-report depression subscale from the short-form Depression, Anxiety, and Stress Scale (DASS-21 [38]) will be used. Each item is rated on a four-point scale from 0 (did not apply to me at all) to 3 (applied to me very much, or most of the time). The DASS-21 is a valid and reliable method of assessing core depressive symptomatology (low positive-affect, anhedonia, lack of motivation, low self-esteem and hopelessness), possesses good psychometric properties [48], and has been validated for use with young adults [49].

#### Secondary outcome measures

Recent meta-analytic results have indicated improvements across a number of domains of psychological wellbeing as a result of reminiscence-based therapy [15]. To assess the generalizability of these changes to young adults some of these will be used as secondary outcome variables. Across the following measures, participants will respond to 11-point, end-defined scales. Meaning in life will be measured using the presence subscale of the Meaning in Life Questionnaire [49], which comprises five items and has good psychometric properties [50]. Higher scores indicate a stronger sense of personal meaning. Self-efficacy will be measured using the eight-item New General Self-Efficacy Scale [51]. This scale measures general perceived competence underlying task or domain-specific self-efficacy using eight items, whereby higher scores indicate a stronger sense of general self-efficacy. The New General Self-Efficacy Scale is psychometrically strong, and has demonstrated superiority over other measures of general self-efficacy [52]. Self-esteem will be measured using a short-form, five-item version of the Rosenberg Self-Esteem Scale [53]. This short-form version has good internal reliability [42], and retains the measurement fidelity of the full scale [54]. Higher scores on this scale indicate higher levels of perceived self-worth.

Two additional secondary outcome measures will be assessed. Firstly, given the therapeutic aims of this intervention, it is reasoned that increases in optimism and positive future-orientation may be possible outcomes. To assess for this, a short-form, three-item version of the Life Orientation Test – Revised [55], consisting of the three positively worded items will be used. This test has demonstrated good psychometric properties [55], with high internal reliability also reported for the short-form version [43]. Higher scores on this scale indicate more positive generalized outcome expectancies. Secondly, as some previous trials of reminiscence-based therapies have also been shown to produce significant reductions in anxiety symptoms [56,57], this will also be assessed. The anxiety subscale on the DASS-21, which measures core symptoms of autonomic arousal, will be used to assess anxiety. The anxiety subscale of the DASS-21 shares the same scale design as the depression subscale, and also its sound psychometric properties.

#### Qualitative data

In addition to collecting demographics and outcome measures, one-to-one interviews with participants from the cognitive-reminiscence condition will also be conducted following completion of the final session of therapy. As the use of a reminiscence-based therapy is somewhat novel in young adult populations, the addition of qualitative data will provide richer, more detailed information regarding participants’ phenomenological account of the intervention. A semistructured interview schedule will be used to collect in-depth information on participants’ experiences. Open-ended questions with inductive probing will be used to answer research questions, such as what participants’ experience of the intervention was like, how they perceived the main task of discussing past events and experiences in their lives, which aspects they found helpful or unhelpful, whether the intervention produced any changes for them, their attitude towards the length of the intervention, and what they might like to see included that was not. To reduce the potential for bias, the interviews will be conducted by a researcher outside of the research team responsible for the trial. Interviews will be conducted with participants until data saturation is reached, or all willing participants have been interviewed.

#### Analysis

Baseline characteristics (demographic, clinical and wellbeing variables) will be compared using chi-square analyses for categorical variables and *t* tests for continuous variables. For the primary and secondary outcomes, repeated-measures ANOVAs will be conducted, along with appropriate post-hoc analyses. Effect sizes will be calculated using Cohen’s *d*, which is based on the pooled standard deviation, along with 95% confidence intervals. To assess individuals for clinically significant change on the primary outcome and distinguish between improved, unchanged and deteriorated cases, the reliable change index will be used [58]. Analyses will be conducted on post-treatment data using intention-to-treat methods presented in the CONSORT guidelines [59], with appropriate imputation of missing data. Qualitative data will be analyzed using applied thematic analysis techniques [60]. Interviews will be transcribed, coded and grouped into themes using an iterative process, and then the themes will be refined and interpreted. Quantitative data reduction techniques will also be used to analyze the frequency of particular attitudes and agreement or disagreement with specific questions, such as whether participants thought the intervention was long enough.

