## Methods and design

### Study design

To evaluate the effectiveness of cognitive-reminiscence therapy in the treatment of young adults with depressive symptoms, we will conduct a randomized controlled trial and compare this intervention with usual care. We will utilize a between-within, repeated-measures design over five time-points (baseline, three weeks into the intervention, post-intervention, one month post-intervention, and three months post-intervention) to assess for both within-group change and differences between these groups in change.

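### Baseline depression is one of five outcome levels in the repeated-measures ANOVA; using it as a covariate, with one pre-named between-arm contrast, would use the same data more efficiently

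*Protocol article*

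**What the plan says.** The Analysis section of the protocol article fixes the method for every quantitative outcome: "For the primary and secondary outcomes, repeated-measures ANOVAs will be conducted, along with appropriate post-hoc analyses". The Study design section describes a "between-within, repeated-measures design over five time-points (baseline, three weeks into the intervention, post-intervention, one month post-intervention, and three months post-intervention"), so baseline is one level of the time factor. The purpose given there is "to assess for both within-group change and differences between these groups in change".

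The Sample size section uses the same framework. It sets 15 participants for the within-group aim, and then, "To assess for a small-to-moderate interaction effect between groups and time", 32 participants (16 per group) at α 0.05, power 0.80 and a correlation of 0.5 among repeated measures. The between-group test is therefore the group-by-time interaction, with (2 − 1) × (5 − 1) = 4 degrees of freedom.

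The Analysis section also plans Cohen's d with 95% confidence intervals, and significance tests comparing the arms at baseline. The article does not mention adjusting the outcome analysis for baseline, and does not single out a visit or contrast as primary.

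**The concern.** In a randomised trial the arms have the same expected baseline score. Treating that score as a fifth outcome level discards this knowledge: the interaction must estimate a baseline difference whose true value is zero, and its error is carried into every comparison. Conditioning on baseline uses the score to explain later variation instead. With 16 evaluable participants per arm, a gain from data already collected is worth having, since the article itself lists the small sample among its limitations.

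The second issue is what the test answers. A 4-df interaction asks whether the two profiles differ in any way. The article's second research question is how effective the therapy is in comparison with usual care. A single adjusted contrast, chosen in advance, answers that directly and settles which comparison carries the result.

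**Working it through.** **Inputs from the Sample size section:** two arms, n = 16 per arm, m = 5 visits, ρ = 0.5, α = 0.05 two-sided.

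**Assumptions, because the article gives effect sizes only in words:** peak effect 0.8 SD, compound symmetry, normal scores, complete data on 16 per arm.

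**1. The plan's own figure.** For the interaction, λ = f²·N·m/(1 − ρ), with 4 and 4(N − 2) df. With f = 0.20 (assumed), λ = 0.04 × 32 × 5 / 0.5 = 12.8 on 4 and 120 df. Power is 81.4% and the required N is 32, as stated. Any f from 0.197 to 0.204 returns 32.

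**2. Planned interaction for a given effect pattern δ.** λ = (n/2)·Σ(δₜ − mean δ)²/(1 − ρ) over five visits. Step pattern, δ = 0.8 × (0,1,1,1,1): the sum is 0.64 × (4 − 16/5) = 0.512, and λ = 8 × 0.512 / 0.5 = 8.19. Power is 60%.

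**3. Baseline-adjusted joint test of the four later visits (4 df).** After conditioning on baseline, each visit has variance 1 − ρ² = 0.75, and each pair has covariance ρ − ρ² = 0.25. Then λ = (n/2)·2·[Σδ² − (Σδ)²/6]. Step pattern: 8 × 2 × 0.64 × (4 − 16/6) = 13.65. On 4 and about 120 df, power is 84%.

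**4. Baseline-adjusted single contrasts (t, 29 df).**
- One visit: SE = √(0.75 × 2/16) = 0.306, and 0.8/0.306 = 2.61. Power is 71%.
- Mean of four visits: variance (1 + 3ρ)/4 − ρ² = 0.625 − 0.25 = 0.375, SE = √(0.375 × 2/16) = 0.217, and 0.8/0.217 = 3.7. Power is 95% for the step pattern.

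**5. Power by pattern** (the multipliers of 0.8 SD are for the four post-baseline visits in order):

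| Pattern | Planned interaction | Adjusted joint test | Adjusted mean of four | Adjusted post-intervention |
|---|---|---|---|---|
| Step (1, 1, 1, 1) | 60% | 84% | 95% | 71% |
| Half, then full (0.5, 1, 1, 1) | 60% | 80% | 88% | 71% |
| Linear (0.25, 0.5, 0.75, 1) | 48% | 62% | 61% | 24% |
| Late (0, 0, 1, 1) | 80% | 84% | 43% | 5% |
| Fade (0.5, 1, 0.5, 0) | 53% | 62% | 43% | 71% |

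The adjusted joint test is ahead in every row. Neither single contrast is.

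**6. Sensitivity to correlation (step pattern).** At ρ = 0.3 the interaction has 44%, the adjusted post-intervention contrast 63% and the adjusted mean 94%. At ρ = 0.7 they have 84%, 87% and 98%.

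**7. Sensitivity to the covariance model.** Step 3 uses compound symmetry, as the plan's calculation does. If both tests estimate an unstructured covariance, the λ values stay the same and the error df fall to 27 (interaction) and 26 (adjusted). In the row order of the table, power is then 53 v 78%, 53 v 73%, 43 v 55%, 73 v 78% and 47 v 55%. These formulas ignore the small cost of chance baseline imbalance. A 20,000-trial simulation of the adjusted unstructured test gives 77, 72, 53, 76 and 54%, and the order is unchanged. If an unstructured adjusted test is set against an ANOVA that assumes sphericity, the advantage disappears for the late pattern (76–78% v 80%) and is negligible for the fade pattern.

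**The case against.** The strongest objection is that the plan is coherent. Aim, test and sample size all concern the group-by-time interaction, and the stated N reproduces. That stands. A reader might infer that the plan names no between-group effect, but the Study design and Sample size sections do name it. A reader might also infer that the analysis yields no direction or size, but Cohen's d with 95% confidence intervals is planned.

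A second objection is that the power ranking depends on the effect pattern. This holds for any single contrast, so the documents do not support saying that a post-intervention contrast is simply better. It targets one visit, and the article says the several visits are there partly to detect when change occurs and whether it is maintained. The objection does not defeat baseline adjustment itself, which is ahead under every pattern tried when the covariance assumptions match. Nor is the interaction the least efficient option: for the step pattern, set so that the interaction has 80% power, an unadjusted change score at post-intervention has 77%.

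A reader might also infer inflated error rates. Four unprotected independent tests would give 1 − 0.95⁴ = 18.5%, and an uncorrected ANOVA under decaying correlation about 7%. The article specifies neither four ungated comparisons nor an uncorrected F test, and independence conflicts with its own correlation of 0.5. Sphericity correction and post-hoc adjustment may properly sit in an analysis plan that is not shown. The planned baseline tests add little, but dropping them would change no primary result.

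Finally, an article may leave model detail to the full plan. Here, however, the method is stated and the trial is sized on it, so the point concerns a choice that was made and not an omission.

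**Conclusion.** The point holds as a recommended efficiency improvement, not as an error. At 16 per arm, ρ = 0.5 and an assumed 0.8 SD effect under compound symmetry, moving baseline from outcome level to covariate raises the power of the joint between-arm test from 48–80% to 62–84% over the patterns tried. The gain is 24 points for the step pattern and 4 to 5 points for the late one.

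A single adjusted contrast can gain much more, or lose. The mean of four visits has 88–95% if the effect is full by post-intervention, 61% under linear growth, and about 43% if the effect fades or appears late. The post-intervention contrast has 71% if the effect is full by then, 24% under linear growth and 5% under late onset. The documents do not settle which pattern to expect, so they do not determine which contrast should be primary.

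The figures assume complete data on 16 per arm. The gain of the post-intervention contrast over the interaction shrinks as the correlation rises.

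**What to change.** Replace the repeated-measures ANOVA for the primary outcome with a mixed model for repeated measures of the four post-baseline DASS-21 depression scores, with arm, visit, arm × visit and the baseline score as covariate. State the covariance structure. Analyse each secondary outcome in the same way with its own baseline.

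Name one baseline-adjusted between-arm contrast as primary, either the mean over the post-baseline visits or the post-intervention visit, and report it with its 95% CI. The remaining contrasts are secondary. The sponsor should make this choice before outcome data are seen, on the pattern of effect it considers most plausible, and give its reason.

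The cost is analysis-plan wording; no extra data or visits are needed. The real downside is committing in advance to one contrast whose power depends on a pattern not yet known. If the sponsor will not commit to a pattern, the adjusted joint test over the four visits is the safer alternative to the planned interaction, though it does not by itself give a single effect estimate.
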